## 1.5 Treatment volume

Especially in the case of re-irradiation, toxicity should be taken into account. For this reason, a policy with diameters not exceeding 5cm and small margins is performed in practice. However, since the maximum safe ReRT volume is unknown, this may lead to undertreatment of patients with larger tumors. In the study of Shen et al. with a median ReRT volume of 202cc, volume was not associated with differences in side effects or survival such that larger volume might not be an appropriate exclusion factor for patients who may otherwise be appropriately treated with ReRT [27]. In the current study the maximum accepted GTV for ReRT will be 125cc (about 6cm diameter). This corresponds to the 90th percentile of the patients re-irradiated in the UMC Utrecht and Groningen study [21]. Several studies performed ReRT in gliomas including or beyond this volume as well for hypofractionated [12, 13, 16–19] as normofractionated regimens [9, 25, 28]. A clinical target volume (CTV) margin of 1 cm will be used to treat the potentially microscopic tumor cells in this zone. A lower dose administered to this zone could limit the risk of radionecrosis and

other adverse events, while a simultaneous integrated boost (SIB) to the contrast enhanced area on T1 MRI may kill tumor cells more effectively.

This phase II clinical trial, -- comparing a 4 fractions regimen with a SIB (experimental arm) to a conventional generally accepted schedule with 10 fractions of 3.5 Gy (retrospective arm) -- will establish the efficacy and safety of these dose prescription methods in tumor with a diameter of up to 6cm (~ 125cc).

## 2. OBJECTIVES

### 2.1 Primary Objective:

The primary objective is to determine if ReRT in 4 fractions is non-inferior to 10 fractions in the primary endpoint of survival after ReRT. Secondary, superiority will be tested.

### 2.2 Secondary Objective(s):

1. To compare progression free survival between the two treatment groups.
2. To describe health-related quality of life (HRQoL) in the experimental treatment group
3. To assess neurocognitive functions in a subgroup of the treatment group.
4. To describe toxicity in the experimental treatment group, and compare grade  $\geq 3$  toxicity in both groups.
5. To establish and compare recurrence patterns on MRI between the two treatment groups.

### 3. STUDY DESIGN

The original 2019 RISING-trial (RISING trial A) was designed as an open label, randomized, non-inferiority, phase III trial with 1:1 allocation for 130 patients. In this trial 13 patients were included in the experimental arm and 16 patients were included in the control arm. The updated 2023 RISinG trial (RISING trial B) is designed as a phase II, multi-center, clinical trial with a historic control group. The additional recruitment period of this phase will be approximately 30 months with an active follow-up time of 12 months.

The 13 patients of the RISING trial A will be supplemented until a total of 66 patients is reached. These patients fulfilling the inclusion criteria will get the following treatment:

- Hypofractionated radiotherapy with SIB in 2 weeks  
4 fractions of 7.5 Gy SIB to the GTV  
And 4 fractions of 5.5 Gy to the CTV (GTV + 5mm margin).

We will compare the survival of this group with a retrospective control group of patients, subtracted from the retro-RISinG registry study, a multi-center retrospective nation-wide population based cohort study, in which details of patient-, tumor- and treatment-related data of all patients with a recurrence of a primary brain tumor since January 2002 up to December 2022 in the Netherlands will be collected. We will select 99 matched patients in total with the following treatment:

- Moderately hypofractionated radiotherapy in 2-3 weeks  
10 fractions of 3.5 Gy to the CTV (GTV + 5 mm margin)

An overview of the target volume definitions and dose prescriptions is presented in table A3 in section 1.8 of the Appendix.

This control group will be matched to the patients in the experimental arm on an individual level for:

1. Age;
2. Gender;
3. WHO-grade primary tumor;
4. Time interval in between first radiation and re-irradiation;
5. MGMT-status.

[figure not shown]

## 4. STUDY POPULATION

### 4.1 Population

Patient enrollment in the experimental arm (arm 1) continues until 66 adult patients with recurrent gliomas eligible for re-irradiation are recruited **in total** (RISING A & B) in the participating hospitals. The recruitment period will be approximately 30 months with an active follow-up time of 12 months.

The control group of the original RISinG study (A) had 16 patients. An additional 83 patients will be selected from the retro-RISING study, a multicenter retrospective nation-wide population-based cohort study, in which details of patient-, tumor- and treatment –related data of patients with a recurrence of a primary brain tumor since January 2002 up to December 2022 in the Netherlands will be collected for arm 2. Out of the retro-RISING trial, we will select only the patients with a treatment schedule of 10x3.5Gy. These patients will be individually matched to the patients in the experimental arm.

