### 4.4 Sample size calculation

The sample size required to achieve a power of  $1-\beta = 0.80$  for the one-sided chi-square test at level  $\alpha = 0.05$  when the hazard ratio is actually 0.90, and a distribution of 40% in the intervention group and 60% in the control group, amounts to 165 subjects: 99 in the control group and 66 in the treatment group [30]. The non-inferiority ratio is 1.4. Unfortunately, there are no historical randomized placebo-controlled trials for arm 2 to use to formulate a margin, therefore we collect this data now as well for matched patients. This ratio is based on clinical judgment of the calculated survival fractions at the proposed non-inferiority margins and published survival data [21].

To clarify the meaning of this non-inferiority margin in practice, the non-inferiority margin specific survival fraction at median survival time could be calculated. This non-inferiority margin means in practice that at least 76% of the patients surviving at the median survival

time of the control group would have survived when treated with the experimental treatment. In other words, at least 38 percent of the patients in the intervention group reach the median survival time instead of 50 percent in the control group.

Expected event rate at the minimal follow-up time of 12 months is 0.7 based on the literature [21, 31]. However, a part of the study population may have a longer follow-up period of even up to 3.5 years. It is anticipated that the proportion of subjects observed with the event during the total study period is 0.8. These results assume that the hazard ratio is constant throughout the study and that Cox proportional hazards regression or the non-inferiority log rank test is used to analyze the data. To compensate for any drop-outs or slight deviation from the assumptions made, the total sample size should be 130 patients (10% added to the calculated sample size).

A point of discussion is that we anticipated that the hazard ratio is actually 0.90, however we can in fact not know the actual hazard ratio. It is justified to assume a hazard ratio below 1.0 when hypothesizing that the tumor will be treated slightly better by a higher dose per fraction.

**Table 1. Number of patients to include to achieve a power of 0.80 with a non-inferiority ratio of 1.4 at a decrease rate of 0.80 for different alfa-levels and actual hazard ratios.**

| Alfa/HR | 0.8 | 0.9 | 1.0 |

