#### 6.1.3 Other study parameters

In addition, KPS will be recorded in the experimental arm 1 and molecular analysis on prior surgically acquired tumor tissue, as well as at the time of recurrence (if available), will be performed.

### 6.2 Study procedures Arm 1

After obtaining informed consent (for details, see section 9.2), patients will receive treatment and necessary follow-up procedures. During the course of the study, participating centers will collect baseline characteristics, technical data such as MRI's, CT's and treatment plans and date of death. Medical imaging will be uploaded to a radiological database at a FTP server. Central data collection exists of HRQoL assessment, toxicity, anti-edema therapy and performance status. Central data collection will be performed by the study team by phone call, or via digital or paper questionnaires. Study procedures are summarized in Table 3. Patients will complete HRQoL questionnaires and the study team will record toxicity and anti-edema treatment by phone call at baseline and at 2, 4, 6, 13, 26, 39, and 52 weeks from the start of ReRT or until disease progression (whichever is sooner). During the first 6 weeks HRQoL will be assessed using the EQ-5D-5L. At subsequent time points QLQ-C15-PAL and BN20+2 will be completed digitally or on paper. Clinicians will be asked to record toxicity, KPS and anti-edema therapy use during regularly scheduled consults.

In case of suspicion of progression, recurrence or radionecrosis on MRI without consensus of diagnosis by the tumor board a FDG-PET, FET-PET or spectroscopy may be used to differentiate but is not mandatory.

IDH-1/2 mutation and MGMT-methylation will be determined at baseline using prior surgically acquired tissue, when molecular analysis has not been performed before, as well as at the time of recurrence (if available).

Any clinical follow-up data after 12 months will be uploaded at time of death, if known.

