#### 8.1.1 OS and PFS

All statistical tests for the efficacy endpoint OS and PFS will be performed according to intention-to-treat (ITT) principle, which is the most unbiased method. Considering the trial being a non-inferiority trial, which is more sensitive to bias, a secondary per-protocol (PP) analysis will be done for OS [43]. The PP analyses will be performed on a “subset of patients who complied sufficiently with the protocol, such as exposure to treatment, availability of measures and absence of major protocol violations” according to the ICH E9 guidelines. The ITT analysis includes all participants. Start date of ReRT will be used as time is 0. Patients not known to have died during the study will be censored for OS at the day they were last known to be alive. Patients free from progression and alive at the last visit will be censored for PFS at the day of last assessment. Endpoints are measured from the first date of re-irradiation.

Distributions of OS and PFS will be estimated by the Kaplan-Meier method. The OS rates at one year, PFS rates at six months and medians of OS and PFS will be presented with two-sided 95% confidence interval(CI) computed using the log-log transformation.

To minimize the effect of confounding when estimating the difference between the treatment and retrospective control group, stabilized inverse probability of treatment weighting (SIPTW) using propensity scores will be applied when comparing the groups on OS and PFS.

Propensity scores will be estimated using logistic regression including important covariates for OS and PFS: primary histology, GTV, KPS and age.

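### Controls are matched at an uneven ratio on five factors, but the weighted analysis ignores the sets and omits gender, re-irradiation interval and MGMT, so imbalance in these goes uncorrected

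*Protocol*

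**What the plan says.** Section 3 describes a nationwide registry in which data "of all patients with a recurrence of a primary brain tumor since January 2002 up to December 2022 in the Netherlands will be collected". From it, "We will select 99 matched patients in total with the following treatment", namely 10 fractions of 3.5 Gy. Matching is at the level of the individual, on age, gender, WHO grade of the primary tumor, interval between first radiation and re-irradiation, and MGMT status.

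Section 4.1 counts differently: 16 controls come from trial A and 83 from the registry. Of the registry patients it says: "These patients will be individually matched to the patients in the experimental arm".

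The total comes from section 4.4, where a 40/60 split "amounts to 165 subjects: 99 in the control group and 66 in the treatment group".

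For the analysis, section 8.1.1 states that "stabilized inverse probability of treatment weighting (SIPTW) using propensity scores will be applied when comparing the groups on OS and PFS". It names the propensity covariates as primary histology, GTV, KPS and age. Sections 8.1.1.1 and 8.1.1.2 add Cox models adjusted through the propensity score, and log-rank tests. None of these sections mentions matched sets or set weights. The number of eligible registry patients on 10 x 3.5 Gy is not given.

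**The concern.** Matching is the only step that addresses gender, re-irradiation interval and MGMT. Matching with one control for some patients and two for others balances these factors only if set size is carried into the analysis. Otherwise the profiles that receive second controls are over-represented among the controls, even when every match is perfect. Weighting individuals on other covariates can also disturb whatever balance the matching achieved.

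The protocol itself treats the omitted factors as prognostic. Section 1.1 cites two cohorts that adjusted for time interval, and section 1.4 links MGMT methylation to outcome. At stake is the non-inferiority conclusion against the 1.4 margin, which in a non-randomized comparison rests on the adjustment.

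**Working it through.** **1. The plan's own figure.** Inputs from section 4.4: true HR 0.90, margin 1.4, one-sided alpha 0.05, power 0.80, 40/60 split, event proportion 0.8.

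- Events = (z0.95 + z0.80)² / (0.4 × 0.6 × [ln(0.9/1.4)]²) = (1.645 + 0.842)² / (0.24 × 0.4418²) = 131.96.
- Patients = 131.96 / 0.8 = 164.95, so 165 = 66 + 99. This reproduces the protocol.
- At 1:1 the same formula gives 158.4, in line with the 159 in Table 1.

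**2. Set sizes.** If each treated patient gets one or two controls:

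| Controls : treated | Ratio | Sets at 1:1 | Sets at 1:2 |
|---|---|---|---|
| 99 : 66 (section 3) | 1.50 | 33 | 33 |
| 83 : 66 (section 4.1) | 1.26 | 49 | 17 |
| 83 : 53 (new patients only, 66 − 13) | 1.57 | 23 | 30 |

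No reading gives a constant whole number.

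**3. What uneven sets do if unweighted.** Take 99:66, a factor present in half of the treated patients (33), and perfect matching within sets. If a share f of the factor-positive patients get two controls, prevalence among controls is 33(1 + f)/99. That is 50% at f = 0.5, 53% at f = 0.6 and 67% at f = 1.

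**4. The two factor lists.**

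| Factor | Matched (section 3) | In propensity score (section 8.1.1) |
|---|---|---|
| Age | yes | yes |
| WHO grade | yes | at most indirectly, through primary histology |
| Gender | yes | no |
| Re-irradiation interval | yes | no |
| MGMT | yes | no |
| GTV, KPS | no | yes |

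**5. Possible size of the bias (assumed inputs).** Suppose 30% of arm 1 (19.8 of 66) have a long interval, with survival HR 0.6 versus short, and each gets exactly one control. The bias factor is approximated by the ratio of mean hazards. In arm 1 the mean is 0.3 × 0.6 + 0.7 = 0.88. The standard error of the log HR is 1/√(0.8 × 66 × 99/165) = 0.178.

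- *All 99 matched:* controls hold 19.8/99 = 20% long interval, with mean hazard 0.2 × 0.6 + 0.8 = 0.92. Factor = 0.88/0.92 = 0.957. False non-inferiority rate at true HR 1.4 = Φ(−1.645 − ln(0.957)/0.178), about 8%.
- *Only 83 matched, the 16 trial A controls taken at 30%:* controls hold (19.8 + 4.8)/99 = 24.8%, with mean hazard 0.248 × 0.6 + 0.752 = 0.901. Factor = 0.88/0.901 = 0.977. False rate about 6.5%.

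If long-interval patients received the second controls instead, the bias would reverse.

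**6. Power under the alternatives.** Power = Φ(ln(1.4/0.9) × √(0.8 × 66m/(66 + m)) − 1.645) for m controls, at true HR 0.90:

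- m = 99: 80.0%; m = 150: 84.9%; m = 200: 87.3%. These are before precision lost to weighting.
- Keeping 99 with each control weighted by 1/(controls in its set): effective number = (33 × 1 + 66 × 0.5)² / (33 × 1 + 66 × 0.25) = 66²/49.5 = 88, and power is about 78.3%.

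**The case against.** Variable-ratio matching is a legitimate method, and the protocol never promises a constant ratio. Ratio, caliper and set weights are details that a statistical analysis plan commonly supplies. No rule says who gets a second control; if second controls were spread evenly over profiles, uneven set sizes alone would cause no imbalance. The 66 + 99 meets 80% power on the protocol's own inputs. All of this stands, and it makes the illustration in step 5 an extreme case, not a prediction.

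It does not answer the mismatch of factor lists. The matching factors and the propensity covariates are both written into the protocol, and they differ. A team that follows section 8.1.1 as written adjusts for neither gender, interval nor MGMT. Correlation with age or histology might remove part of an imbalance, but nothing ensures it.

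Three stronger inferences are tempting and not supported:

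- **That the matching cannot be done.** It can, with unequal sets.
- **That eligible controls are thrown away and power is lost.** This needs more than 83 eligible registry patients. Extrapolating section 1.1 (13 centers × 2 to 6 patients a year × 21 years = 546 to 1,638) with an assumed 10% to 30% share on 10 x 3.5 Gy gives 55 to 491, before the arm 2 criteria are applied. That range includes no surplus at all.
- **That controls without a recorded MGMT status are dropped.** Section 6.2 says for arm 1 that "IDH-1/2 mutation and MGMT-methylation will be determined at baseline using prior surgically acquired tissue". It says nothing about what the registry holds, and the protocol does not call for exact matching.

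**Conclusion.** The point holds as an inconsistency between design and analysis. Sections 3 and 4.1 imply unequal matched sets on five factors. Section 8.1.1 carries neither the sets nor three of those factors, so imbalance in gender, interval or MGMT would remain in the primary comparison.

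Size and direction of the bias cannot be known from the protocol. Under the assumed extreme allocation the HR is multiplied by about 0.96 to 0.98 and the false non-inferiority rate is about 6.5% to 8% instead of 5%. This rests on the 30% prevalence, the HR of 0.6, no second controls for those patients, and no correction through correlated covariates.

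The sample-size calculation is not in error. A gain in power is conditional on more than 83 eligible registry patients and should be presented that way.

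**What to change.** In sections 3, 4.1 and 8.1.1:

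- Estimate one propensity score on the union of the two lists: age, gender, WHO grade/primary histology, re-irradiation interval, MGMT, GTV and KPS, with a stated approach for unknown MGMT status.
- Apply it to all registry patients who meet the arm 2 criteria, with 99 controls in total as a minimum and not a cap.
- Reconcile sections 3 and 4.1 on whether the 16 trial A controls are part of the matching.

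The cost is protocol wording, chart checks for any additional controls, and a control number not fixed in advance. No patient is added to arm 1 and no procedure changes. If no surplus of controls exists, the balance is still repaired.

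If 99 matched controls are kept, weight each by 1/(number of controls in its set) and state the price: an effective 88 controls and about 78.3% power, before further loss from propensity weighting. The wider covariate list is needed in that case too.

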### 4.2 Inclusion criteria

In order to be eligible to participate in study arm 1 and 2, a subject must meet all of the following criteria:

- Supratentorial recurrent high-grade glioma with contrast enhancement on CE-T1.
- The gold standard is histological evidence of a recurrence. When a surgical procedure to acquire this evidence is not desirable or possible, a recurrence may be diagnosed by radiological imaging alone, taking the following in consideration:
  - Agreement of the tumor board or a consultant neuro-radiologist that imaging changes are in keeping with recurrence.
  - An interval of no less than 3 months since last (chemo)radiotherapy.

- Utilization of the RANO criteria for tumor progression [29].
- If needed, additional imaging sequences such as PET and perfusion MRI.
- Unifocal glioma (i.e. lesions clustering around residual surgical cavity).
- Prior course of treatment including radiotherapy with an EQD2 ( $\alpha/\beta = 2$ ) of at least 47Gy.
- Age  $\geq 18$  years.
- Karnofsky Performance Score 60 or above.
- Ability of subject to understand character and individual consequences of the clinical trial (arm 1).
- Patients who received re-irradiation for the recurrence of a primary brain tumor with a treatment schedule of 10x3.5Gy (arm 2).

### 4.3 Exclusion criteria

A potential subject who meets any of the following criteria will be excluded from participation in this study (arm 1 and 2):

- Previous re-irradiation or prior radiosurgery or prior treatment with interstitial radioactive seeds.
- CE-T1 tumor diameter greater than 6cm ( reflecting a spherical tumor of 125cc).
- Time interval of less than 6 months after prior radiotherapy.
- Time interval of less than 3 weeks after last re-resection (1 week for biopsy).
- Known carcinoma < 3 years ago (excluding Carcinoma in situ of the cervix, basal cell carcinoma, squamous cell carcinoma of the skin) requiring immediate treatment interfering with study therapy.
- Women with childbearing potential without adequate contraception.

If a patient is not eligible for arm 1 based on the MRI results (e.g. T1-CE diameter >6 cm, reflecting a spherical tumor of 125 cc), these non-eligible patients are being replaced by new patients. These non-eligible patients are not included in the statistical analysis of the trial and treated with the physicians' choice.

### 4.4 Sample size calculation

The sample size required to achieve a power of  $1-\beta = 0.80$  for the one-sided chi-square test at level  $\alpha = 0.05$  when the hazard ratio is actually 0.90, and a distribution of 40% in the intervention group and 60% in the control group, amounts to 165 subjects: 99 in the control group and 66 in the treatment group [30]. The non-inferiority ratio is 1.4. Unfortunately, there are no historical randomized placebo-controlled trials for arm 2 to use to formulate a margin, therefore we collect this data now as well for matched patients. This ratio is based on clinical judgment of the calculated survival fractions at the proposed non-inferiority margins and published survival data [21].

To clarify the meaning of this non-inferiority margin in practice, the non-inferiority margin specific survival fraction at median survival time could be calculated. This non-inferiority margin means in practice that at least 76% of the patients surviving at the median survival

time of the control group would have survived when treated with the experimental treatment. In other words, at least 38 percent of the patients in the intervention group reach the median survival time instead of 50 percent in the control group.

Expected event rate at the minimal follow-up time of 12 months is 0.7 based on the literature [21, 31]. However, a part of the study population may have a longer follow-up period of even up to 3.5 years. It is anticipated that the proportion of subjects observed with the event during the total study period is 0.8. These results assume that the hazard ratio is constant throughout the study and that Cox proportional hazards regression or the non-inferiority log rank test is used to analyze the data. To compensate for any drop-outs or slight deviation from the assumptions made, the total sample size should be 130 patients (10% added to the calculated sample size).

A point of discussion is that we anticipated that the hazard ratio is actually 0.90, however we can in fact not know the actual hazard ratio. It is justified to assume a hazard ratio below 1.0 when hypothesizing that the tumor will be treated slightly better by a higher dose per fraction.

**Table 1. Number of patients to include to achieve a power of 0.80 with a non-inferiority ratio of 1.4 at a decrease rate of 0.80 for different alfa-levels and actual hazard ratios.**

| Alfa/HR | 0.8 | 0.9 | 1.0 |
|----------------|------------|------------|------------|
| 0.05    | 99         | 159        | 274        |
| 0.10    | 72         | 116        | 200        |

The trial is primarily designed to show non-inferiority, in addition superiority will be tested. If the actual hazard ratio is lower, the patient number will be sufficient to detect superiority (Table 2).

**Table 2. Number of patients to include to achieve a power of 0.80 at a decrease rate of 0.80 for different alfa-levels and actual hazard ratios for superiority analysis.**

| Alfa/HR | 0.4 | 0.5 | 0.6 | 0.7 | 0.8 |
|----------------|------------|------------|------------|------------|------------|
| 0.025   | 47         | 82         | 151        | 308        | 787        |
| 0.05    | 37         | 65         | 119        | 243        | 621        |
| 0.10    | 27         | 47         | 87         | 178        | 453        |

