## **6.5 Replacement of individual subjects after withdrawal**

In section 4.4 the sample size calculation for this study is given. Therefore, an inclusion of 65 subjects per study group is aimed to generate a total of 130 patients. If a subject in arm 1 discontinues from the study prematurely the reason, if given, must be fully evaluated and recorded appropriately.

If a patient who has signed informed consent withdraws for any reason before randomization, the patient will be replaced. These patients are not included in the statistical analysis. After randomization, patients withdrawing because of any reason will not be substituted by additional patients. Patients withdrawn from the trial retain their identification codes (e.g. randomization number), if already given. New patients must always be allotted a new identification code.

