##### 8.1.1.1. OS

The hazard rate for the experimental versus the retrospective control group and its two-sided 80 and 95% CIs will be estimated using a Cox proportional hazards model. We will adjust for confounding using propensity scores.. Omission of 4 fractions as non-inferior to 10 fractions of radiotherapy if the higher 90% CI of the hazard ratio (HR) of 4 fractions versus 10 fractions was not above 1.4.

Only when non-inferiority has been demonstrated, we will test for superiority of the experimental treatment in a hierarchical fashion, using Kaplan-Meier method and two-sided log-rank test at a significance level  $\alpha = 10\%$  in ITT analysis.

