The most objective toxicity terms will be evaluated, including central nervous system necrosis, edema and seizures. Maximal accepted percentage grade 3 to 5 radiotherapy related acute toxicity or late radionecrosis (severe symptoms; medical intervention indicated) is 30%. Maximal accepted percentage grade 4 or 5 adverse events is 20%. Maximal accepted percentage grade 5 adverse events is 10%. Toxicity terms are graded according to the CTCAE v5.0 (Appendix 1.0). Edema will be graded similar to radionecrosis.

If maximal tumor diameter has to be modified to 5 cm, expected loss of recruitment amounts 15% based on the retrospective dataset of UMC Utrecht and UMC Groningen. The recruitment time should be prolonged with approximately 5 months to achieve a total of 65 patients.

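### Section 4.4 ends at 130 patients after a claimed 10% addition, yet its own calculation gives 165, and the operative 66 + 99 contains no allowance for loss

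*Protocol*

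**What the plan says.** Section 4.4 sets up the non-inferiority calculation "for the one-sided chi-square test at level" 0.05, with power 0.80, "when the hazard ratio is actually 0.90", a margin of 1.4, and 40% of patients in the intervention group and 60% in the control group. The result "amounts to 165 subjects: 99 in the control group and 66 in the treatment group". The proportion of patients with an event is taken as 0.8. The decision rule in section 8.1.1.1 agrees with that alpha: non-inferiority is accepted "if the higher 90% CI of the hazard ratio (HR) of 4 fractions versus 10 fractions was not above 1.4", and the upper limit of a 90% interval corresponds to one-sided 0.05.

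Later in the same section, as compensation for drop-outs and small departures from the assumptions, the text says that "the total sample size should be 130 patients (10% added to the calculated sample size".

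The smaller figure recurs. Section 6.5 says that "an inclusion of 65 subjects per study group is aimed to generate a total of 130 patients" and ties its replacement rule to randomization. Section 8.3, on the longer recruitment needed if the diameter limit is lowered, speaks of prolonging it "to achieve a total of 65 patients".

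Sections 3 and 4.1 set the targets for the current design: 66 in arm 1, including 13 from trial A, and 99 controls, made up of 16 from trial A and 83 from the registry. Section 3 describes 130 patients at 1:1 as the design of trial A.

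**The concern.** Adding 10% to 165 cannot give 130. One section therefore states two totals for the primary test, and the one said to include the allowance is the smaller.

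Two things are at stake. First, sections 6.5 and 8.3 apply the superseded number to the replacement rule and to recruitment after a possible restriction. Second, section 4.4 says that protection against loss is needed and presents it as built in. If the enrolled 66 + 99 is just the uninflated result, that protection does not exist, and the 80% power holds only in the no-loss case.

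**Working it through.** **Inputs, all from section 4.4.** One-sided alpha 0.05 (z = 1.645); power 0.80 (z = 0.842); true hazard ratio 0.90; margin 1.4; allocation 0.4 / 0.6; event proportion 0.8.

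**Step 1: reproduce 165.**
- Log distance: ln(1.4 / 0.9) = 0.4418; its square is 0.1952.
- Events = (1.645 + 0.842)² / (0.4 × 0.6 × 0.1952) = 131.96.
- Patients = 131.96 / 0.8 = 164.95, rounded up to 165.
- Split 40/60: 66 + 99.

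The plan's figure reproduces exactly, with no drop-out term anywhere.

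**Step 2: apply the 10% that the section describes.**
- 165 × 1.1 = 181.5, so 182.
- 165 / 0.9 = 183.3, so 184.

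Neither route leads to 130.

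**Step 3: where 130 fits.** All six entries of Table 1 ("Number of patients to include to achieve a power of 0.80 with a non-inferiority ratio of 1.4") reproduce under 1:1 allocation. At alpha 0.10 and hazard ratio 0.9 the table gives 116. Adding 10% gives 116 × 1.1 = 127.6 or 116 / 0.9 = 128.9, close to 130. Section 3 gives 130 at 1:1 for trial A. The link to alpha 0.10 is an inference from Table 1; the protocol does not state it. At the current alpha of 0.05 the 1:1 entry is 159, not 165, so the table also still shows the 1:1 allocation.

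**Step 4: compare the operative targets with the calculation.** Sections 3 and 4.1 give 66 + (16 + 83) = 66 + 99 = 165, the bare result of step 1. Nothing has been added.

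**Step 5: power at the stated assumptions.** Power = Φ(0.4418 × √(N × 0.8 × p × (1 − p)) − 1.645), where N is the number of patients contributing full information and p is the arm 1 share.

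| Contributing patients | N | 0.4418 × √(…) | Power |
|---|---|---|---|
| 66 + 99, nobody lost | 165 | 2.487 | 80.0% |
| 59.4 + 99, 10% of arm 1 lost | 158.4 | 2.408 | 77.7% |
| 59.4 + 89.1, 10% of both arms lost | 148.5 | 2.359 | 76.3% |
| 65 + 65, nobody lost (trial A size) | 130 | 2.253 | 72.8% |

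The last row is for comparison only; the current design does not plan it.

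**Step 6: what would restore 80% with 10% of arm 1 lost.** With 59.4 evaluable in arm 1, 118.7 evaluable controls give 80.0%, so about 119 in place of 99.

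**The case against.** The case on the other side has several parts, and some of it stands.

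- **The 80% is correct for the enrolled design.** This stands. A reader might infer from the 130 that the trial is being run at 72.8% power. The documents do not support that: sections 3 and 4.1 govern enrolment and give 66 + 99, section 4.4 opens with the same numbers, and the Summary and section 3 assign 130 at 1:1 to trial A. The gap of 65 against 66 in section 8.3 is one patient.
- **Losing 10% of both arms is pessimistic.** This stands in part. Of the 99 controls, 83 are selected retrospectively and are not exposed to prospective withdrawal. The endpoint is death from any cause, and patients who leave are censored at the last date known alive, so they still contribute. For that reason the arm 1-only figure of 77.7% is given beside 76.3%.
- **Controls may have more events than 0.8.** The registry runs from January 2002 to December 2022, and section 1.1 cites median survival of 7.7 to 11.5 months. As an assumption, take 90% to 95% events in controls and 80% in arm 1, and replace the information term by 1 / (1/d₁ + 1/d₀), where d₁ and d₀ are the events per arm. Power is then 81.6% to 82.2% with no loss and 79.2% to 79.9% with 10% of arm 1 lost. This could offset most of the shortfall, but the plan does not use that assumption. It would have to be stated and justified.
- **Propensity weighting costs further precision.** Section 8.1.1 commits to stabilized weights, and the formula has no term for them. A reader might want to put a lower power figure on this. The protocol gives nothing from which to quantify it, so no figure is given here.

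None of this rescues the sentence giving 130, or supplies the missing allowance.

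**Conclusion.** The point holds as an error in the stated sample size together with a claimed allowance that is absent. The calculation of 165 is right. The 130 in section 4.4, the 65 per group and 130 in section 6.5, and the 65 in section 8.3 are not figures of the current design.

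It would go too far to say that the trial fails to deliver 80% power. It delivers 80.0% under its own assumptions if no information is lost. The supported statement is narrower: section 4.4 plans for a 10% shortfall that 66 + 99 does not cover. The cost is about 2 points of power if only arm 1 loses 10%, and about 4 points if both arms do. These sizes assume a true hazard ratio of 0.90, 80% events in each arm, proportional hazards, lost patients who contribute nothing, and no precision lost to weighting.

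**What to change.** 1. In section 4.4, replace 130 by 165 = 66 + 99 and remove the statement that 10% was added. Say that 165 carries no allowance, and give power as 80% with no loss and about 76-78% with 10% loss.
2. In section 6.5, replace 65 per group and 130 by 66 and 99, and reword the replacement rule, which refers to a randomization that the current design does not have.
3. In section 8.3, replace 65 by 66.
4. Add one sentence saying that the formula has no term for precision lost to propensity weighting. Do not print a figure for it unless data support one.

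If the sponsor prefers a true 10% allowance, the total is 182 to 184 (at 184, about 74 + 110). Drawing about 119 evaluable controls would hold 80% with 59.4 evaluable patients in arm 1 and enrol nobody further. It is an option only if enough eligible, individually matched 10 × 3.5 Gy records exist, which the protocol does not show. It also moves the 40/60 split, so the calculation would have to be restated.

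Items 1 to 4 cost amendment wording and a slightly less favourable power statement. The larger control group would cost about 20 more registry records.
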